### Sample size

#### Power and sample size

Child weight and waist circumference are the primary outcome measures for this study and considered the most difficult outcomes to change. Secondary aims of this intervention are to increase children’s fruit and vegetable consumption and time spent physically active, and to decrease consumption of sweetened drinks and time spent sedentary.

Australian national data [39] report an average weight and waist circumference in 3-year old children of 16.4kg (SD = 2.2kg), and 51.1cm (SD = 3.8cm) respectively [39]. Further, these data report that at this age Australian children consume an average of 85g (SD = 82g) of vegetables (not including potato), 202g (SD = 129g) of fruit and 78mL (SD = 121mL) of sweetened drinks daily. Additionally this group is reported to spend an average of 117min (SD = 30min) being active and 662min (SD = 71min) being sedentary daily [40].

To detect a 5% difference in weight between groups at age three (reducing average weight in the intervention group by approximately 1kg), with Type I and Type II errors of 5% and 20% respectively, the number of subjects required is given by:$$ \mathrm{N}\ \left(\mathrm{number}\ \mathrm{of}\ \mathrm{subjects}\right) = 32/\mathrm{E}\mathrm{S}\ {\left(\mathrm{Effect}\ \mathrm{S}\mathrm{ize}\right)}^2 $$$$ \mathrm{E}\mathrm{S} = \left(\mathrm{mean}\ \mathrm{x}\ \%\ \mathrm{meaningful}\ \mathrm{difference}\right)/\mathrm{standard}\ \mathrm{deviation} $$$$ \mathrm{So},\ \mathrm{N} = 32/0.382 = 223 $$

This sample size will also allow us to detect differences of: 4% in BMI (i.e. 0.66kg/m^2^), 3% in waist circumference (i.e. 1.5cm), 36% in vegetable consumption (i.e. 31g, equivalent to approximately ½ a serve/day); 24% in fruit consumption (i.e. 49g, equivalent to approximately 1/3 of a serve/day); 60% in sweetened drink consumption (i.e. 47mL/day); 10% in active time (i.e. 12min/day) and 4% in sedentary time (i.e. 26min/day).

As this study will randomize by first-time parents groups, we need to take account of within-group clustering and increase our sample size according to the design effect/inflation factor (DEFF). The design effect is given by: DEFF = 1 + [(n-1) x ICC], where n is the number of people in each cluster and the ICC is the intra-class coefficient. Based on our previous experience working with first-time parents groups, we estimate that each cluster contains an average of nine mother-infant pairs, and the ICC is estimated to be 0.1 (based on data from the Melbourne InFANT Program), thus the design effect is 1.8. We will also adjust our sample size to account for estimated attrition over the three years of the study (<25%).

Therefore, our final sample size is: (223 x 1.8) / 0.75 = 535. To achieve an equal number of groups in each arm of the trial (mean number of participants in groups = 9), we will aim to recruit 540 participants from a total of 60 first-time parents’ groups (30 groups and 270 participants in each arm of the trial).

The CONSORT flow diagram is outlined in Fig. 1.

**Fig. 1 Fig1:**
[figure not shown]
CONSORT flow diagram

### Intervention group

The intervention arm will receive the previously trialed Melbourne InFANT Program delivered in first-time parent groups until child is aged 18-months. The intervention content has been reported elsewhere [24, 35] and is outlined in the background in this paper. In the current InFANT Extend Program, the Melbourne InFANT Program content will be largely replicated however some enhancement, informed by both quantitative [24] and qualitative [41] outcomes will be incorporated (e.g. parent's desire for more practical strategies for preparing food and playing with children). To reflect the transition in technology preference of parents over the time since the Melbourne InFANT Program was trialed (2008–2010) we plan to alter some aspects of program delivery. While the original Program content was delivered in groups with the aid of a DVD (which parents took home), in the present study DVDs will no longer be used and all content will be made available online via dedicated webpages. The use of webpages provides opportunities previously not afforded, to monitor website use and thus inform at a group level, the dose of intervention received.

In addition, during the first 18 months, the original Melbourne InFANT Program will be extended by the addition of first-time parent group Facebook® (Menlo Park, CA, USA) Pages. On-line engagement will be restricted to the individual first-time parent group, and will be mediated by the group facilitator, a nutrition expert, for up to one hour per week. This use of social media is anticipated to promote parent engagement between their regular social meetings, and to provide opportunities to: share their child feeding and activity related outcomes (knowledge, questions, successes, challenges); enable the group facilitator to provide support; and to reiterate program messages.

As in the original Melbourne InFANT Program, parents will be mailed one newsletter each quarter. These newsletter were well received in the original program and provided an important opportunity, given the infrequency of intervention sessions (three monthly), to engage mothers and to reinforce key program messages. This aspect of the program will be modified and extended in the InFANT Extend Program and will form the key focus of the extended intervention. Group delivery beyond 18 months is not feasible given we know that first time parent groups – the site of delivery - are often not sustained after this time [36]. Furthermore, our previous experience highlighted that while attendance to 18 months was relatively high, attendance figures began to decline at around 12 months of age. Therefore, in the current study, the Melbourne InFANT Program content will be reiterated and extended through delivery of intervention messages via six emailed newsletters (3 monthly from child age 18 months to 3 years). Newsletters will contain web links directing participants to specifically designed content within the Melbourne InFANT Program website (discussed below). This content will seek to reinforce and build upon skills and knowledge developed in the group-delivered intervention. It will also introduce new knowledge and skills known to be of relevance to parents in the promotion of healthy eating and physical activity behaviors across the often behaviorally challenging toddler years. In addition, participants will be reminded of newly developed toddler focused content on the Program website through monthly emails and Facebook® posts. The focus of each intervention session (3–18 months) and each newsletter provided in the extension (21–36 months) is outlined in Table 1.

**Table 1 Tab1:** Intervention time-frame and focus for the InFANT Extend Program

Infant age	Emerging behaviours	Anticipatory guidance intervention focus (group, newsletters, Facebook® to 18 months; newsletters and Facebook® 18–36 months)
3mo	Early weaning and introduction of solids. Introduction of nutrient poor foods. Parents development of a feeding style	To support parents to delay weaning/introduction of solids to around 6 months To provide basic principles related to best practice in early feeding To introduce basic concepts regarding parental feeding styles and how these might relate to beliefs about parenting.
6mo	Adoption by parents of a feeding style and TV viewing habits Food rejection by infants	To develop parents’ understanding regarding: *feeding styles and impact on children’s eating *basic nutrition principals * sedentary behaviours in families To introduce national recommendations for no screen exposure (television viewing) until 2 years of age and reasons for this To develop parents’ understanding of ‘normal’ food rejection and how to interpret and manage
9mo	Increasing use of TV Parents’ increased awareness of child mobility. Infant crawls and pulls self upright and walks with handhold	To develop understanding regarding: * parental modeling of eating, sedentary and physical activity behaviours * impact of eating, activity and sedentary behaviours on health of children and adults and the provision of opportunities to promote healthy eating and engagement in play
12 mo & 15 mo & 18 mo	Increasing autonomy of child in eating and activity Infant stands without support and beginning to walk	Continued development of themes/skills regarding: * eating and moving for health – parents and children * how to feed/how to manage food rejection and demands * providing fail-safe food and activity environments
21,24,27,30,33,36 mo	Child independence in activity and feeding; desire to be in control and to choose	Continued development of themes/skills regarding: * eating and moving for health – parents and children * how to feed/how to manage food rejection and demands Practical strategies for incorporating more active play into family routines Development of fundamental movement skills through everyday play * providing supportive food and activity environments

Key: mo - months

### Control group

The control group families will receive usual care from their MCHn. In addition, these families will be sent general health newsletters (e.g. dental health, sun protective behaviours, general safety) every three months across the child’s first three years (11 newsletters in all). Consistent with the intervention group, control group participants will receive birthday and Christmas cards. These families’ participation will be acknowledged with gifts (to a maximum value of $15.00) on receipt of completed questionnaires.

### Data collection

#### Measures

As outlined in Table 2, parent and infant data will be collected at 3, 18 and 36 months. Standard demographic and socio-economic information will be collected by parental report at baseline (3 months). Additional measures to be collected are detailed below.

**Table 2 Tab2:** Measures and time-frame for the study

Intervention timeline - year		1	2				3	4
Measures		Infant age						
		3 months	6 months	9 months	12 months	15 months	18 months	36 months
Dietary intake	Parent Child	✓ ✓		✓*			✓ ✓	✓ ✓
Sedentary behaviour	Parent Child	✓		✓ ✓			✓ ✓	✓ ✓
Physical activity	Parent Child	✓		✓ ✓			✓ ✓	✓ ✓
Family food environment	Parent	✓		✓			✓	✓
Family physical activity & sedentary environment	Parent	✓		✓			✓	✓
Demographic data	Parent	✓						
Anthropometric data	Parent Child	✓ ✓		✓ ✓			✓ ✓	✓ ✓

*Modified FFQ

#### Primary measures

##### Child’s anthropometry

Height, weight and waist circumference will be measured by study staff who will undergo training with a paediatrician specialized in clinical nutrition. Recumbent length (in infants) will be assessed using a calibrated length mat/height and from standing age will be assessed using a calibrated stadiometer. Waist circumference (minimum circumference between the rib cage and iliac crest) will be measured using a non-stretchable tape measure at 18 and 36 months of age. BMI z score will be calculated using WHO growth standards [42].

#### Secondary measures

##### Child’s dietary intake

Children’s dietary intake will be assessed at 18 months and 3 years with a parent completed food frequency questionnaire. This 79 item FFQ has been used within the original InFANT Program and is currently being validated against the three days of 24 h recall also collected in that study when children were 18 and 36 months of age. Data will be analyzed using an in-house, specially designed database using the 2007 Australian Food and Nutrient Database (AUSNUT) Database [43]

### Measurement of physical activity and sedentary behaviours

Seven days of objectively assessed physical activity data will be collected using accelerometers at 18 and 36 months. At this time children will be fitted with an ActiGraph accelerometer which they will wear for eight consecutive days (which will capture weekday and weekend day activity and sedentary patterns) [44]. ActiGraph monitors are small, light and unobtrusive and are worn on a belt around the waist. This methodology was successfully employed during the original InFANT Program intervention when children were aged approximately 19 months. ActiGraph counts correlate (up to r = 0.70) with energy expenditure estimated by direct observation and doubly-labelled water respectively, among 3–5 year old children [45, 46] and correlate highly (r = 0.87) with energy expenditure estimated by indirect calorimetry among children [47]. Counts will be recorded at 15-s epochs to accurately capture the sporadic and intermittent activity patterns of young children. Data will be downloaded and then reduced to total counts/day, minutes/day and percentage of time spent sedentary, and in light-, moderate- and vigorous-intensity physical activity using age-appropriate cut points [48]. In addition, indirect measures of children’s physical activity will be assessed by parental report including: parental engagement in physically active play and the number of hours the child typically spends playing outdoors on weekdays and weekend days.

In addition, parents will be asked to indicate how much time (hours/min) their child usually spends watching television/DVD and playing electronic games on a typical weekday (Monday-Friday) and on a typical weekend day (Saturday and Sunday) and to estimate the amount of time spent in situations that restrict movement (e.g. stroller, playpen) at 3, 9, 18 and 36 months. Test-retest reliability of these items in a previous study ranged from ICC = 0.5–0.9 [49]. Parental reports of their child’s “usual” TV viewing has been shown to correlate with both videotaped observations of the child’s TV viewing [50] and with parental diaries of viewing [51].

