### Study participants and recruitment

The recruitment process for the InFANT Extend Program will largely replicate that used in the original Melbourne InFANT Program [24, 35]. An important exception relates to the local government area (LGA) recruitment strategy. To seek to address the over representation of university educated women in the Melbourne InFANT Program [24] seven relatively disadvantaged Victorian LGAs will be purposively recruited. These LGAs will selected by the group level variable *Index for Socio Economic Disadvantage* (IRSD) [37] such that all will be in the lowest tertile of disadvantage (i.e. most disadvantaged). It is important to note that there will be distinct areas of greater and lesser socioeconomic advantage within each LGA and these are indicated by the IRSD of postcode regions within each LGA. For practical reasons, each LGA will sit within a 75km radius of the research center (Geelong, Victoria, Australia).

Eighty percent of eligible first-time parents’ groups (rounded to next even number to ensure equal within LGA allocation to control and intervention groups) within each of these LGAs will be randomly selected and approached by research staff for recruitment during one of the standard nurse-facilitated group sessions. Individual parents will be eligible to participate if they give informed written consent, are first-time parents and are literate in English. Infants with chronic health problems likely to influence height, weight, levels of physical activity or eating habits will be excluded from analyses but will be permitted to participate in the program.

Parent groups will be eligible if eight or more parents choose to enroll in the study. To facilitate inclusion of participants experiencing disadvantage, groups commencing in MCH centres considered relatively socioeconomically disadvantaged (as determined by the post code of the region within each LGA), will be eligible if six or more parents enroll. When first-time parents’ groups decline to participate, the next randomly selected group within the LGA will be approached. Non-consenting parents within participating groups will be permitted to attend the intervention sessions, but will not be required to provide data or be contacted by the research team in any other way.

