Randomization of first-time parents’ groups (clusters) to intervention or control will occur after recruitment to avoid selection bias [38]. Randomization (stratified by LGA) will be conducted by an independent statistician. While parents will not be blinded to allocation, they will not be informed of the study aims or hypotheses and the recruiting emphasis will focus on promoting healthy eating and active play from the start of life. Staff measuring height and weight will not be blinded to intervention status as they will deliver the intervention, however, data entry and analyses will be conducted with staff blinded to participant’s group allocation.

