### Statistical analyses

Intervention effects will be assessed based on intention to treat principles and taking into account the cluster-based sampling design. Generalized Estimating Equations [61] using the xtgee function in Stata, will be used to fit longitudinal regression models enabling comparison of primary outcome variables between intervention and control groups, adjusted for baseline values where appropriate (infants were not consuming foods nor mobile at baseline, i.e. 3 months of age, hence adjustment for diet or physical activity variables is not possible).

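### Season of measurement is largely shared within a parents' group but enters neither the stratification nor the stated adjustment, an avoidable loss of precision on secondary accelerometer outcomes

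*Protocol article*

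**What the plan says.** All references are to the protocol article.

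- **Timing.** Measurement of physical activity and sedentary behaviours sets accelerometry by child age: "Seven days of objectively assessed physical activity data will be collected using accelerometers at 18 and 36 months". The monitor is fitted once per visit, "which they will wear for eight consecutive days", so that weekdays and weekend days are both covered. The same section has parents report "the number of hours the child typically spends playing outdoors on weekdays and weekend days". Season, calendar month and day length are not mentioned anywhere.
- **Clusters.** The unit of randomization is the first-time parents' group. The Background says that in the parent program such groups started sessions when infants were about three months old, and baseline here is also at 3 months.
- **Stratification.** Study participants and recruitment: "Randomization (stratified by LGA) will be conducted by an independent statistician". Equal allocation is arranged within each LGA. No other balancing factor is named.
- **Analysis.** Statistical analyses: "Intervention effects will be assessed based on intention to treat principles and taking into account the cluster-based sampling design". The model is a GEE, adjusted for baseline values where appropriate. Because infants were neither eating foods nor mobile at 3 months, "hence adjustment for diet or physical activity variables is not possible".
- **Role of the outcomes.** More active time and less sedentary time at 18 and 36 months is a secondary objective. Power and sample size gives detectable differences for both.

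**The concern.** If infants in a group are of similar age and each is measured at a fixed age, most of a group wears the monitors at about the same time of year. Any seasonal effect on movement is then a cluster-level effect and adds to between-cluster variance, the component that most limits precision in a cluster trial. Season is a convenient covariate: it follows from birth date and visit age, is unaffected by allocation, and needs no baseline measurement. It is therefore available for exactly the outcomes for which the article says baseline adjustment cannot be made. At stake is power for accelerometer-measured active and sedentary time.

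**Working it through.** **The plan's own figures.** From Power and sample size: N = 32/ES². With ES rounded to 0.38 (the printed 0.382 reads as 0.38 squared), 32/0.38² = 221.6, against 223 stated. DEFF = 1 + (9 − 1) × 0.1 = 1.8. Final N = 223 × 1.8/0.75 = 535.2, matching 535. At N = 223 the detectable ES is √(32/223) = 0.379, or 0.379 × 30 = 11.4 min active (12 stated) and 0.379 × 71 = 26.9 min sedentary (26 stated). The plan's figures reproduce closely enough to build on.

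**Inputs for season.**
- From the article: active time mean 117, SD 30 min/day; 10% difference = 11.7 min/day; ICC 0.1; nine per group; 60 groups; 540 recruited, 25% attrition, so 540 × 0.75 = 405 analysed.
- Assumed, because the article gives nothing: a sinusoidal seasonal effect, fully shared within a group, with a peak-to-trough swing of 10, 20 or 30 min/day, added on top of the ICC of 0.1.

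**Formulas.** Variance without season is 30² = 900, of which 90 is between and 810 within groups. Season adds (swing/2)²/2 to the between-group part: 12.5, 50 or 112.5. With k groups of size m per arm, SE = √[2(between/k + 810/(mk))] and power = Φ(11.7/SE − 1.96).

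The answer depends on how attrition falls. Losing whole groups leaves 405/2/9 = 22.5 groups of 9 per arm. Thinning every group leaves 30 groups of 9 × 0.75 = 6.75.

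| Swing (min/day) | Between variance | ICC | DEFF (m = 9) | SE, 22.5 × 9 | Power | SE, 30 × 6.75 | Power |
|---|---|---|---|---|---|---|---|
| 0 | 90 | 0.10 | 1.80 | 4.00 | 83.3% | 3.74 | 87.8% |
| 10 | 102.5 | 0.11 | 1.90 | 4.14 | 80.7% | 3.85 | 85.9% |
| 20 | 140 | 0.15 | 2.18 | 4.52 | 73.5% | 4.16 | 80.2% |
| 30 | 202.5 | 0.20 | 2.60 | 5.10 | 63.1% | 4.64 | 71.3% |

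(The 73.5% is 73.49% before rounding, hence 73% in whole per cents.)

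**Sedentary time.** Here season is given as a share s of total variance, with SD held at 71: SE² = 2 × 71² × [0.10 + s + (0.90 − s)/9]/22.5. For 26 min/day, power is 0.78 at s = 0, and 0.77, 0.73, 0.70 and 0.63 at s = 0.01, 0.03, 0.05 and 0.10.

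**If the ICC of 0.1 already contains season.** Planned power is then unaffected, and adjustment takes the seasonal part out of the 90. For a 10 min swing, 90 − 12.5 = 77.5, SE = √[2(77.5/22.5 + 4)] = 3.86, power 85.8%. For a 20 min swing, 90 − 50 = 40, SE = √[2(40/22.5 + 4)] = 3.40, power 93.1%. A 30 min swing cannot fit inside this ICC, since 112.5 exceeds 90.

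**The case against.** **It belongs in the SAP.** The GEE sentence names primary outcome variables, activity is secondary, and covariates for secondary outcomes are often settled in an analysis plan, which is not shown here. This has force and lowers the urgency. It does not dispose of the point: the same sentence takes up adjustment for physical activity and stops at saying that a baseline value is unavailable, and LGA as sole stratifier is fixed in the article.

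**There is no validity problem.** Correct. A reader might infer that unbalanced seasons bias the comparison. They do not: groups are randomized, so season is independent of arm in expectation. Chance imbalance is not a further harm either, because shared seasonal variation is part of the between-group variance that a cluster-adjusted analysis already puts into the standard error. Visits 18 months apart do place a group in roughly opposite seasons, but this applies to both arms alike and does not distort the contrast between them.

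**The premise is inferred.** Also correct. A reader might take it that every child in a group is measured in one season. The article gives neither the spread of birth dates within groups nor visit windows, so a group may straddle seasons. Only *largely shared* is supported.

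**The size is unknown.** Correct. The swing is assumed, and a 30 min swing equals a full SD. The article does not say which outcome the ICC of 0.1 describes. It comes from an earlier trial in the same kind of groups, so it may already include season.

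**Too broad a claim.** A reader might conclude that these outcomes can be adjusted for nothing at all. The article rules out only baseline diet and physical activity values. Screen time is reported at 3 months, so it has a value to adjust for, and it is asked as usual viewing; the case there is weak. Outdoor play is asked as what is typical, so a seasonal effect is less certain than for accelerometry.

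**Conclusion.** The point holds as one of efficiency on secondary accelerometer outcomes. The article combines age-anchored visits, LGA-only stratification and a stated adjustment that it says cannot serve physical activity, and so leaves a known, treatment-independent source of cluster-level variance in the error term.

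With season on top of the ICC of 0.1, the loss for active time is about 2 to 3 percentage points of power at a 10 min swing, 8 to 10 at 20 min and 17 to 20 at 30 min, depending on whether attrition thins groups or removes them. In the thinned case a 20 min swing still leaves 80%. Sedentary time starts at 0.78 in the nine-per-group calculation and has no slack. If the ICC already includes season, the loss against plan is nil and adjustment is a gain. All of this rests on an assumed sinusoidal swing fully shared within groups; straddling of seasons would shrink it. Under either reading of the ICC, adjustment improves precision if activity varies with season.

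**What to change.** In Statistical analyses, prespecify season of measurement at each visit as a covariate in the models for accelerometer outcomes, or confirm that the SAP already does so. Use either calendar quarter (three degrees of freedom) or sine and cosine of day of year (two). Derive it from the scheduled date, that is, birth date plus 18 or 36 months, so that it is fixed at randomization. Outdoor play may be treated the same way as an option; for screen time there is little case. The randomization need not change.

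The cost is two or three degrees of freedom in secondary models. No new measurement should be needed: the article does not say that dates are recorded, but WHO BMI z-scores require age at measurement, so they should be derivable.
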